**To evaluate safety of sarilumab as compared to SOC**

Safety through day 29

- Cumulative incidence of serious adverse events (SAEs)
- Cumulative incidence of Grade 3 and 4 adverse events (AEs).

Serious adverse events (SAEs).  
Grade 3 or 4 Adverse events (AEs).

|                                                                                                                                                   |                                                                                                                                    |
|---------------------------------------------------------------------------------------------------------------------------------------------------|------------------------------------------------------------------------------------------------------------------------------------|
| To evaluate differences in the effect of sarilumab on the serum levels of inflammatory cytokines in patients infected with COVID-19.       | Changes in serum level of CRP, IL-6, lymphocyte count, neutrophils count, d-dimer, LDH, ferritin, coagulation tests                |
| To evaluate differences in the proportion of patients showing more than >1 organ failure, e.g. cardiovascular, liver and kidney failure | Patients showing more than >1 organ failure through day 15                                                                         |
| To identify prognosis factors of sarilumab efficacy related to laboratory parameters or disease features                                   | Focused medical history, demographic characteristics, COVID-19 history, concomitant medication, and laboratory disease parameters. |

## 5. DESIGN OF THE STUDY

This is an exploratory phase II, multicenter, open-label, randomized clinical trial to evaluate the efficacy and safety of an early intervention with sarilumab + methylprednisolone (or equivalent CS dose) plus SOC vs methylprednisolone (or equivalent CS dose) plus SOC alone in patients with COVID-19 pneumonia aimed to prevent progression to severe respiratory failure, ICU admission, or death.

Experimental arm: Sarilumab + methylprednisolone (or equivalent CS doses) plus SOC for COVID-19

Control arm: methylprednisolone plus SOC for COVID-19.

Sarilumab will be administered intravenously following this posology:

-Patients <75kg body weight: single 200mg SARILUMAB dose (1 single-dose pre-filled syringe containing 200 mg sarilumab in 1.14 ml solution (175 mg/ml) added to 100 mL 0.9% sodium chloride for a 1-hour intravenous infusion).

-Patients ≥75kg body weight: single 400mg SARILUMAB dose (2 single-dose pre-filled syringes, each containing 200 mg sarilumab in 1.14 ml solution (175 mg/ml) added to 100 mL 0.9% sodium chloride for a 1-hour intravenous infusion).

Corticosteroids will be given to all patients at a 1mg/kg/d of methylprednisolone (or equivalent CS dose) for at least 3 days.

SOC includes [esing](#) weight adjusted corticosteroid doses plus any drugs that are being used in clinical practice (e.g. lopinavir/ritonavir; hydroxy/chloroquine, and other than those used as part of another clinical trial

Randomization will be 1:1 to any of the treatment groups and will be stratified per center.

For patients on will be rescued with sarilumab at the same doses and be included in a 15-day open-label follow up phase or until hospital discharge, ICU admission or death.

Clinical follow-up visits will be performed at 3, 5, and 15 days after treatment randomization.

Patients in any treatment group progressing to severe respiratory failure fulfilling criteria for treatment with anti-IL6 inhibitors according to clinical practice guidelines, as defined by the presence of Brescia-COVID 2-3 plus inflammatory markers, will be considered treatment failures for the sake

of the primary analysis and be rescued according to local treatment protocols, which may include tocilizumab. Patients in the control group (SOC group without sarilumab) progressing to Brescia-COVID 2-3 plus inflammatory markers, will be given the option to be rescued with sarilumab at the same doses and, in that case, be included in an open-label phase and be followed up for two additional weeks (with visits at 3, 7 and 15 days after sarilumab rescue administration).

A final follow-up visit will be conducted for all patients at D29 from randomization, regardless of initial treatment assignment.

Figure 1 – Graphical study design

[figure not shown]

Figure 2 – Graphical study design OPEN-LABEL PHASE

[figure not shown]

## 6. SCREENING AND SELECTION OF STUDY SUBJECTS

### *Inclusion Criteria*

1. Informed consent prior to performing any study procedure. Witnessed oral consent will be accepted in order to avoid paper handling. Written consent by patient or representatives will be obtained whenever possible.
2. Male or female adult patients of at least 18 years of age.
3. The patient is positive for SARS-CoV-2 by real-time PCR or other validated tests
4. The patient is hospitalized for COVID-19 without either mechanical ventilation (invasive or non-invasive) or oxygen mask with reservoir bag and at least one of the following:
  - Radiographic evidence of pulmonary infiltrates by imaging (chest x-ray, CT scan, etc.),
  - OR
  - Clinical assessment (evidence of rales/crackles on exam) AND SpO2  $\leq$  94% on room air that requires supplemental oxygen.
5. More than 7 days between the onset of symptoms (fever, cough, and/or dyspnea) and treatment administration day. In the absence of fever, cough, or dyspnea, other symptoms like asthenia, headache, or gastrointestinal symptoms may be considered.
6. The patient present progressive elevation of inflammatory parameters suggestive of a hyperinflammatory syndrome :
  - Presence of elevated IL-6 ( $>40$  pg/mL)
  - or
  - Elevated d-dimer ( $>1.0$  mcg/ml), or alternatively, progressive worsening in at least two of these inflammatory parameters in the prior 24-48h: CRP, LDH, serum ferritin, lymphopenia, or d-dimer.
7. Patient must be, in the investigator opinion, able to comply with all the protocol procedures.
8. Negative pregnancy test in case of fertile women

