| Duration of study              | The observation period will be from randomization until 28 days after randomisation, hospital discharge, ICU admission or death, whichever occurs first.                                                                                                                                                                                                                                                                                                                                                                                                                                                                                                                                                                                                                                                                                                                                                                                                                                                                                                                                                                                                                                                     |
| General design and methodology | 
A multi-center, randomized, clinical trial with two arms to study the efficacy and safety of early treatment with sarilumab plus SOC compared to standard of care (SOC) in patients with COVID-19 pneumonia (BCRSS score 1).
 
Experimental arm: Sarilumab + methylprednisolone (or equivalent doses) plus SOC for COVID-19
 
Control arm: Methylprednisolone (or equivalent doses) plus SOC for COVID-19.
 
Randomization will be 1:1 to any of the treatment groups and will be stratified per center.
 
Methylprednisolone 1mg/kg/day (or corticosteroid dose equivalents) for at least 3 days.
 
SOC includes any drugs that are being used in clinical practice (e.g. lopinavir/ritonavir; hydroxy/chloroquine, and other than those used as part of another clinical trial) according to each site local protocol.
 
Patients will be followed up to four weeks after randomization.
 
Patients randomized to the control arm (CS + SOC group without sarilumab) progressing to severe respiratory failure fulfilling criteria for treatment with anti-IL6 inhibitors according to clinical practice guidelines, as defined by the presence of Brescia-COVID
 |

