#### 4. TRIAL OBJECTIVES

##### *Primary Objective*

The overall objective of the study is to evaluate the efficacy of an early intervention with sarilumab in the prevention of progression to severe respiratory failure/ICU admission or death in COVID-19 infected patients with pneumonia and regular oxygen supplement requirements (Brescia-COVID- 1).

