### ***Exclusion Criteria***

1. Patients with high oxygen requirements including face mask with reservoir, non-invasive mechanical ventilation or high flow nasal cannula, or mechanical ventilation.
2. Patients admitted at the ICU
3. Participation in any other clinical trial of an experimental treatment for COVID-19.
4. In the opinion of the clinical team, progression to death is imminent and inevitable within the next 24 hours, irrespective of the provision of treatments.
5. Any hypersensitivity or allergy to the administration of sarilumab or corticosteroids.
6. Current treatment with immunosuppressive or any immunomodulatory medication within 8 weeks of baseline.
7. Patients who have received immunosuppressive antibody therapy within the past 5 months, including intravenous immunoglobulin
8. AST/ALT values > 10 x ULN
9. Neutropenia (< 0.5 x 10^9/L).
10. Severe thrombocytopenia (< 50 x 10^9/L).
11. Sepsis caused by an alternative pathogen.
12. Diverticulitis with risk of perforation.
13. Ongoing infectious dermatitis.
14. Patients with another active infection, including localized infections.
15. Pregnant or breast-feeding females will be excluded

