| 2                                        | Oxygen therapy plus 1 of the following criteria:
a) The patient has dyspnoea or STACCATO SPEECH (inability to count rapidly to 20 after taking a deep breath) at rest or after minimum activity (sitting down on bed, standing up, speaking, swallowing, coughing)
b) Respiratory rate > 22 with >6L/minute O 2
c) PaO 2 <65mmHg with >6L/minute O 2
d) Significant worsening of chest x-ray (increased compactness and extension of infiltrate) |
| 3                                        | The patient requires high-frequency nasal ventilation (HFNC), CPAP or NIV                                                                                                                                                                                                                                                                                                                                                                                                                     |
| 4                                        | The patient is intubated for CPAP or pressure support                                                                                                                                                                                                                                                                                                                                                                                                                                         |
| 5                                        | The patient is under controlled mechanical ventilation; PaO 2 /FiO 2 >150 mmHg                                                                                                                                                                                                                                                                                                                                                                                                 |

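### The stated population is Brescia-COVID 1, but no eligibility criterion requires that score, so patients at Brescia 2 or Brescia 0 can be randomised

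*Protocol*

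**What the plan says.** **Target population.** The Primary Objective (protocol section 4) concerns patients with "pneumonia and regular oxygen supplement requirements (Brescia-COVID- 1". The synopsis row on general design describes treatment "in patients with COVID-19 pneumonia (BCRSS score 1". The synopsis objective and Table 1 name the same score.

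**Eligibility (section 6).** Inclusion criterion 4 admits hospitalised patients "without either mechanical ventilation (invasive or non-invasive) or oxygen mask with reservoir bag and at least one of the following". The first alternative is "Radiographic evidence of pulmonary infiltrates by imaging (chest x-ray, CT scan, etc", with no oxygen condition attached. Only the second alternative, crackles with low saturation "on room air that requires supplemental oxygen", brings in an oxygen need. Exclusion criterion 1 removes "Patients with high oxygen requirements including face mask with reservoir, non-invasive mechanical ventilation or high flow nasal cannula, or mechanical ventilation". ICU patients are excluded separately. No criterion in section 6 or in the synopsis refers to a Brescia score.

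**Scale (Appendix 6).** Level 0 is ambient air and level 1 is oxygen therapy. Level 2 is "Oxygen therapy plus 1 of the following criteria", where the items are (a) dyspnoea or staccato speech at rest or on slight activity, (b) and (c) a raised respiratory rate or low PaO2 on more than 6 L/min, and (d) significant worsening of the chest x-ray. High-flow cannula, CPAP and NIV are level 3.

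**Endpoint and rescue.** The primary endpoint is progression to Brescia 2 or more, ICU admission or death. Control patients who progress to Brescia 2-3 with inflammatory markers may receive sarilumab as rescue (synopsis; sections 5 and 8).

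**The concern.** Screening decides eligibility by the inclusion and exclusion criteria (section 8, Screening and Inclusion). Naming the population in the objective does not keep other patients out.

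The more important gap is at Brescia 2. Such an entrant stands at the endpoint threshold, and at the Brescia level named for control-arm rescue, on the day of randomisation. Read one way, the outcome is fixed before treatment in either arm. Read the other way, where progressing requires a change from baseline, the respiratory-failure component cannot occur for that patient. The protocol does not choose. Either way these patients carry little or no information about the treatment effect.

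There is also a question of purpose. The rationale is to treat earlier than current use, which it says is prioritised to Brescia 2-3, and efficacy at Brescia 2 or more is a separate open-label objective. Randomising Brescia 2 patients mixes the two questions. At the other end, Brescia 0 patients fall outside the stated objective and probably have a lower event risk.

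**Working it through.** **Step 1: who can enter.**

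| Patient | Criterion 4 | Exclusion 1 | Brescia score |
|---|---|---|---|
| Room air, infiltrates on imaging | met by imaging alone | not triggered | 0 |
| Ordinary oxygen, no level 2 item | met | not triggered | 1 (target) |
| Ordinary oxygen, item 2a or 2d | met | not triggered; neither item has a flow threshold | 2 |
| Ordinary oxygen above 6 L/min, item 2b or 2c | met | arguable; the phrase on high oxygen requirements is open-ended | 2 |
| High-flow cannula or NIV | n/a | excluded | 3 |

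The other criteria (such as inflammatory markers and symptom duration) are assumed to be met in each row. They do not separate the scores.

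**Step 2: the plan's own figure.** Inputs from section 10: 25% versus 10%, two-sided 5%, power 80%, allocation 1:1. With p̄ = (p1+p2)/2 = 0.175,

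n = [1.96·√(2·p̄(1−p̄)) + 0.842·√(p1(1−p1)+p2(1−p2))]² / (p1−p2)² = 99.5, rounded up to 100 per arm.

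This matches the stated 100 per arm. Power at 100 per arm is 80.2%, from

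power = Φ{[|p1−p2|·√n − 1.96·√(2·p̄(1−p̄))] / √(p1(1−p1)+p2(1−p2))}.

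**Step 3: a share q at Brescia 2 on entry.** The documents give no value for q, so it is assumed. The 25% and 10% are taken to apply to Brescia 1 patients.

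- Reading A, counted as failures: p′ = q + (1−q)·p.
- Reading B, contributing no events: p′ = (1−q)·p.

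| q | A: rates | A: power | B: rates | B: power |
|---|---|---|---|---|
| 1% | 25.75% vs 10.9% | 78% | 24.75% vs 9.9% | 80% |
| 2% | 26.5% vs 11.8% | 76% | 24.5% vs 9.8% | 79% |
| 5% | 28.75% vs 14.5% | 69% | 23.75% vs 9.5% | 78% |
| 10% | 32.5% vs 19.0% | 59% | 22.5% vs 9.0% | 75% |
| 20% | 40.0% vs 28.0% | 43% | 20.0% vs 8.0% | 69% |

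Under A the risk ratio moves from 0.10/0.25 = 0.40 to 0.19/0.325 = 0.58 at q = 10%. Under B it stays at 0.40 and power falls only because there are fewer events. B is an extreme: ICU admission and death remain possible for these patients, so a change-from-baseline rule would not remove every event.

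**Step 4: Brescia 0.** If 20% enter at Brescia 0 with half the risk, the multiplier is 0.8 + 0.2·0.5 = 0.9. The rates become 22.5% versus 9.0% and power is 75%.

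**The case against.** The strongest reply is that the intent is plain. The objective, the design text and Table 1 all say Brescia 1, and the score is taken at V0 and V1, so sites would probably enrol accordingly and any exceptions can be identified in the data. That makes large shares less likely, but it does not create an eligibility rule.

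The Brescia 2 route is also narrower than the scale suggests. The open wording of exclusion 1 can reasonably be read to cover items 2b and 2c, and item 2d needs an earlier film for comparison. That leaves mainly item 2a. Listing dyspnoea among the symptoms in inclusion criterion 5 adds little, because that criterion dates symptom onset and does not describe the patient's state at randomisation. This stands.

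A reader might infer that every Brescia 2 entrant is automatically a failure in both arms, so that reading A is the effect. The documents do not support that: each statement of the endpoint speaks of progressing, which reading B respects. For the same reason, and because inflammatory markers are also required, it does not follow that such a control patient qualifies for rescue at day 0.

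Finally, section 10 does not say which population the 25% and 10% describe. If they describe patients enrolled under section 6 as written, the dilution is already inside them.

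**Conclusion.** The contradiction between the stated population and the criteria is certain from the text. Followed as written, the criteria can enrol patients for whom the main endpoint component is already met or is undefined.

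The size is not known. It rests on an assumed share and on the 25% and 10% rates referring to Brescia 1 patients. At 1-2% the loss is at most about 4 percentage points of power. At 5-20% power is 69% to 43% on the failure reading and 78% to 69% on the no-event reading. The Brescia 0 limb is minor, because those patients can still progress and the endpoint works for them.

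A reader might go further and conclude that the comparison is biased or that the stated power is lost altogether. Neither follows. Allocation is randomised and the Full Analysis Set holds everyone randomised, so such entrants are balanced between arms in expectation and type I error is not inflated. Power is reduced, not removed, and the sample size arithmetic is correct.

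**What to change.** Reconcile the eligibility lists in sections 1 and 6 with the population that the protocol already states: require Brescia-COVID 1 at screening and confirm it immediately before randomisation. The two lists also differ on high-flow cannula, which section 6 excludes by name and the synopsis does not, so they should be aligned in the same edit.

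Define the primary endpoint as progression from baseline score 1 to 2 or more, ICU admission or death. Check that the rescue passages read consistently with that baseline.

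If anyone with another baseline score has already been randomised, keep that patient in the Full Analysis Set, state how the patient is counted, and add a supportive analysis restricted to baseline score 1.

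The cost is one eligibility line and one eCRF check on a score already collected. If the 25% and 10% refer to Brescia 1 patients, the sample size stays at 100 per arm. Some patients become ineligible, which may slow the planned two-month recruitment by an amount the documents do not allow to be estimated.

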### ***Exclusion Criteria***

1. Patients with high oxygen requirements including face mask with reservoir, non-invasive mechanical ventilation or high flow nasal cannula, or mechanical ventilation.
2. Patients admitted at the ICU
3. Participation in any other clinical trial of an experimental treatment for COVID-19.
4. In the opinion of the clinical team, progression to death is imminent and inevitable within the next 24 hours, irrespective of the provision of treatments.
5. Any hypersensitivity or allergy to the administration of sarilumab or corticosteroids.
6. Current treatment with immunosuppressive or any immunomodulatory medication within 8 weeks of baseline.
7. Patients who have received immunosuppressive antibody therapy within the past 5 months, including intravenous immunoglobulin
8. AST/ALT values > 10 x ULN
9. Neutropenia (< 0.5 x 10^9/L).
10. Severe thrombocytopenia (< 50 x 10^9/L).
11. Sepsis caused by an alternative pathogen.
12. Diverticulitis with risk of perforation.
13. Ongoing infectious dermatitis.
14. Patients with another active infection, including localized infections.
15. Pregnant or breast-feeding females will be excluded

## **7. TREATMENT PLAN**

### ***Method of Treatment Assignment***

This is a multicenter, randomized, open label clinical trial evaluating the safety and efficacy of sarilumab (Kevzara®) for the early treatment of the hyperinflammatory syndrome caused by the infection with SARS CoV 2.

Eligible patients shall be enrolled in the study under the supervision of the investigator or designated sub-investigators.

This open-label trial will use blind randomization of patients in a 1:1 ratio to sarilumab (plus corticosteroids) or SOC (plus corticosteroids) through a centralized system embedded in the eCRF (Oracle Clinical). Randomization will be stratified by site.

### ***Dosing and Administration***

Experimental group: Patients in the treatment arm will receive sarilumab plus corticosteroids on top of SOC medication. Sarilumab will be administered intravenously as a single dose following this posology:

- Patients <75kg body weight: single 200mg SARILUMAB dose (1 single-dose pre-filled syringe containing 200 mg sarilumab in 1.14 ml solution (175 mg/ml) added to 100 mL 0.9% sodium chloride for a 1-hour intravenous infusion).
- Patients ≥75kg body weight: single 400mg SARILUMAB dose (2 single-dose pre-filled syringes, each containing 200 mg sarilumab in 1.14 ml solution (175 mg/ml) added to 100 mL 0.9% sodium chloride for a 1-hour intravenous infusion).
- Corticosteroids will be administered intravenously following this posology: Methylprednisolone 1mg/kg/day (or corticosteroid dose equivalents) for at least 3 days

**Control group:** Patients in the control group will receive corticosteroids on top of SOC medication.

Corticosteroid: will be administered intravenously following this posology: Methylprednisolone 1mg/kg/day (or corticosteroid dose equivalents).

SOC: All patients will continue background SOC according to local clinical practice protocols and be followed up until disease progression, patient withdrawal, ICU admission, hospital discharge, loss of follow up, or death.

